### Intervention programs

All participants will take part in their assigned 7-day program and will receive the same advices: staying active, avoiding bed rest, activity modification and reassurance (see Additional file 1.)
*Thermal therapy group:* Participants will be asked to wear a heatwrap over the lower lumbar spine that heats up to 40 °C within 30 min. This temperature is maintained for 8 h [25]. The heatwrap will be worn during the day for 8 consecutive hours on 7 consecutive days.*Thermal therapy + exercises group:* In addition to thermal therapy, participants will be asked to perform 30 min of exercises at home for 5 days. Four different categories of exercises will be given: 1) functional activity exposure (sitting, sit-to-stand, lifting, bending, etc.); 2) exercises targeting trunk muscles (motor and postural control exercises); 3) mobility of the lumbar spine and 4) preferential direction if applicable. The exercises will be selected by a physical therapist (PT) according to a pre-determined list of 23 different exercises (see Additional file 2 [26] and Additional file 3) after assessing the participant’s clinical history and performing a brief physical assessment. Thus each participant will have to perform a program of 3 tailored exercises among the different categories. A fourth exercise can be prescribed if the participant responds favourably to “preferential direction” exercise (meaningful reduction in pain intensity during the exercise). Each exercise will be usually performed for 2 or 3 series of 10 repetitions for a maximum of 30 min per day. Considering that no specific categories of exercises have been shown superior for LBP [6], these exercises have been selected to reflect clinical reasoning and practice.*Control group:* a room temperature heatwrap will be worn during the day for 8 h on 7 consecutive days to control for potential supportive and sensory influence of the heatwrap.

### Outcomes

#### Primary outcome

The primary outcome of this study is disability, and will be evaluated by the ODI French Canadian Version [17]. This self-administered questionnaire contains 10 questions to answer on a 6-point Likert scale (0 = no pain-related disability to 5 = maximal pain-related disability); one to assess pain intensity and nine to determine how pain affects everyday life activities in different domains, for a total of 50 points reported in percentage (0–100%). It presents excellent construct validity (RMDQ) [27] (Pearson coefficient (r) = 0.84) and excellent test-retest reliability (intraclass correlation coefficient (ICC) = 0.92) [17]. As previously mentioned, the MCID for ALBP is 9 points [15].

#### Secondary outcomes

*Pain intensity* will be assessed by asking the participant to rate his average pain over the last 7 days on an 11-point numerical rating scale (NRS): (0 to 10), ranging from “no pain” to “worst imaginable pain” [28]. The NRS is commonly used to measure the effect of interventions in LBP patients [21] and has a MCID of 2 points [28]. Its strong association with the visual analog scale (VAS) (Pearson’s correlation coefficient (r) = 0.93 [20]), supports its excellent construct validity.

*Pain-related fear* will be assessed with the 11-item version Tampa Scale of Kinesiophobia (TSK-11) questionnaire. It measures problematic beliefs and behaviours associated with pain, focusing on beliefs that pain is damaging and that painful movements should be avoided [29]. Each item is self-rated on a 4-point Likert scale (1 = strongly disagree, 4 = strongly agree). The total score ranges from 11 to 44 points, and higher scores represent greater fear of re-injury due to movement [18]. For LBP, TSK-11 has good internal consistency (Cronbach’s alpha = 0.79) and test-retest reliability (ICC = 0.81) and has a standard error of measurement (SEM) of 3 points [18]. The strong correlation with the 17-items Tampa Scale of Kinesiophobia (TSK), r = 0.93, supports its construct validity [18].

*Self-efficacy* will be measured using the Chronic Disease Self-Efficacy Scale - Short-Version (CDSES-6), a 6-item version of the CDSES-33 (a questionnaire with 33 items) that measures the self-efficacy to adopt self-management behaviors and to achieve predefined goals [19]. Each item is self-rated on a scale from 1 (“not at all confident”) to 10 (“totally confident”) and the total score represents the mean of the 6 items. The CDSES-6 has a good internal consistency (Cronbach’s alpha (α) = 0.86) and has an excellent construct validity, demonstrated by a strong correlation with the CDSES-33 (r = 0.91) [19]. It has been proven sensitive to change in people with LBP [19].

*Perception of change* in global LBP condition since the initial assessment will be measured using a single-item question, the Global Rating of Change (GRoC). GRoC is measured on a 15-point Likert scale, ranging from − 7 to + 7, whereas − 7 means “a very great deal worse”, 0 means “about the same” and + 7 means “a very great deal better” [24, 30]. Test-retest reliability for LBP patients is fair to good (ICC = 0.61) [30] and the MCID is 3 points [30, 31].

*The number of steps walked* will be measured with a fitness watch (Garmin Forerunner 15 version 2.70, Garmin International Inc., Olathe, KS, U.S.A.), as a proxy of the level of physical activity. A recent study [32] challenged a similar device, the Garmin Vivofit 2 (Garmin International Inc., Olathe, KS, U.S.A.) to measure the number of steps walked. The results showed that it obtained small mean absolute percentage error values (< 3) for measuring the number of steps walked when compared to a video [33], reflecting its ability to measure accurately the number of steps walked. The fitness watches will be provided by the research center (Cirris.)

### Sample size & statistical analysis

The estimation of the sample size was done with G*Power 3.1.7 considering an effect size = 0.80; α = 0.05, 1- β = 0.80 and lost at follow-up = 10%. The sample size was calculated for the primary outcome (ODI) with data from an unpublished study in our group (*n* = 50 with ALBP), and revealed that 23 participants are required per group. Thus, 69 participants with ALBP will be recruited.

Generalized linear mixed models (GLMM) will be performed for all outcomes. Our GLMM will incorporate terms for Group and Time (0, 1, 4, 12 and 24 weeks), and Group x Time interaction with random effect for participants. The Group x Time interactions will inform if there is a benefit to combine both treatments. If a violation in assumptions allowing the use of GLMM occurs (e.g. a change in the types of data distribution between the different time points), a nonparametric longitudinal data (nparLD) analysis will be performed as this procedure provides robust rank-based methods, even in case of an unknown distribution or atypical measurements and outliers [34]. Both GLMM and nparLD work well with missing data without any need to impute or reject participants. A one-way ANOVA or a non-parametric Kruskal-Wallis ANOVA will be used to compare the effect of intervention on the number of steps walked per day. The significance threshold will be set at *p* < 0.05.

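### The stated inputs do not give 23 per group for a two-sided comparison of two groups; that needs 29, and 69 in total gives about 71% power on that reading

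*Protocol article*

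**What the plan says.** Protocol article, section on sample size and statistical analysis: "The estimation of the sample size was done with G*Power 3.1.7", for the Oswestry Disability Index (ODI), with data from an unpublished study of 50 people with acute low back pain. The inputs are given as "considering an effect size = 0.80; α = 0.05, 1- β = 0.80 and lost at follow-up = 10" per cent. The result is that the calculation "revealed that 23 participants are required per group. Thus, 69 participants with ALBP will be recruited".

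The same section plans generalized linear mixed models with Group, Time (0, 1, 4, 12 and 24 weeks) and their interaction, a rank-based longitudinal analysis as fallback, and a one-way ANOVA or Kruskal-Wallis test for daily steps. It adds: "The significance threshold will be set at *p* < 0.05". It does not say which G*Power test was used, whether the test was one- or two-sided, or whether 0.80 is Cohen's d or Cohen's f. The hypothesis under Objectives and hypothesis is directional (the combination does better than thermal therapy alone and control), but no one-sided test is declared anywhere.

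**The concern.** An effect size of 0.80 given without a symbol is most naturally a standardised difference between two groups, and an alpha of 0.05 given without a side is most naturally two-sided. On that reading 23 per group is too few, even before loss to follow-up.

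This paragraph is the only justification of the trial's size for its primary outcome. If 23 came from a one-sided calculation, the advertised 80% power belongs to a test that the trial does not plan to run. A non-significant ODI result could then be taken as good evidence against a large effect, when a two-sided pairwise comparison would have missed such an effect in roughly three trials out of ten.

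**Working it through.** **Inputs (all from the sample size paragraph).** Effect size 0.80, alpha 0.05, power 0.80, loss 10%, 23 per group, three equal groups. Assumption: 0.80 is d for a comparison of two means.

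**Method.** Two-sample t-test with n per group: noncentrality d√(n/2), degrees of freedom 2n − 2, power from the noncentral t distribution.

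**Reproducing 23.** With a one-sided alpha of 0.05:
- n = 20: noncentrality 0.80 × √10 = 2.53, power 79.9%.
- n = 21: noncentrality 0.80 × √10.5 = 2.59, power 81.7%. So 21 evaluable are needed.
- Loss: 21 × 1.1 = 23.1, or 21/0.9 = 23.3. Both round to 23, although rounding up gives 24.
- Normal approximation: 2 × ((1.645 + 0.842)/0.80)² = 19.3, so 20 evaluable, and 20/0.9 = 22.2, so 23.

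**The same inputs, two-sided.**
- n = 25: noncentrality 2.83, power 79.1%.
- n = 26: noncentrality 2.88, power 80.7%. So 26 evaluable are needed.
- Loss: 26/0.9 = 28.9, so 29 per group and 3 × 29 = 87 in total, against 69. The normal approximation gives 25 evaluable and 28 randomised per group.

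**What 23 per group gives, two-sided, d = 0.80.**

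| Evaluable per group | Power |
|---|---|
| 23 (no loss) | 75.6% |
| 23 × 0.9 = 20.7 | 70.9% |

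With 20.7 evaluable per group, 80% power is reached at d = 0.89.

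**Other readings of 0.80 (three-group one-way ANOVA, power from the noncentral F).**
- f = 0.80: 21 evaluable in total, or 7 per group.
- f = 0.40: 66 evaluable in total for 80% power with equal groups (22 per group, 22/0.9 = 24.4, so 25 randomised). With 63 evaluable the power is 79.8%; with 69 × 0.9 = 62.1 it is 79.1%.
- If one arm differs from the other two by d = 0.80, f is 0.80 × √2/3 = 0.377. This needs 72 evaluable, and 63 evaluable give 74.6%.

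None of these readings gives both 80% power for a non-directional test and 69 randomised with 10% loss.

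**Sensitivity to the analysis.** If a two-group comparison is adjusted for baseline ODI and the baseline-to-follow-up correlation is r, the effective effect is d/√(1 − r²). With r = 0.5 (an assumption), 0.80/√0.75 = 0.924, and 20.7 per group give about 83%. About r = 0.45 is enough for 80%.

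**The case against.** The strongest reply is that 71% is not the power of the planned analysis. It belongs to an unadjusted t-test at one visit, whereas the protocol plans a mixed model over five time points. Its power may be higher or lower, depending on correlations that the article does not report. This stands. A reader might infer that the trial's true power is 71%, and the documents do not support that. The reply does not rescue the paragraph, however, because nothing in it refers to repeated measures or baseline adjustment.

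A second reply is that the one-sided origin is a guess. This stands too. The match requires inflating by 1.1 or rounding 23.3 down, and f = 0.40 with 21 evaluable per group reaches 79.8% and leads to 23 by the same lenient inflation. One-sidedness is therefore a reading consistent with 23 and not an established fact. But f = 0.40 is not what the article states, and applied strictly it needs 66 evaluable.

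Two further inferences are tempting:
- **Power for the minimal clinically important difference.** The article says that "the MCID for ALBP is 9 points [15"], and 9/0.80 = 11.25 would be the matching SD. But it does not say that 0.80 was derived from 9 points, and it gives no SD, so power for 9 points would rest entirely on an assumed SD.
- **Joint power against both comparators.** About 58% is obtained if both pairwise tests must succeed with d = 0.80 each. The protocol states a scientific hypothesis about both comparators but sets no such decision rule.

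Finally, an article may leave the SD and the raw difference to the full protocol, so their absence is not counted here. The mismatch between the printed inputs and the printed result is not an omission of that kind.

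**Conclusion.** Wrong as written. With d = 0.80, alpha 0.05, 80% power and 10% loss, a two-sided comparison of two groups needs 29 randomised per group, not 23: a shortfall of 6 per group, or 18 in total. The figure of 23 is consistent with an undeclared one-sided test, while the planned Group × Time, ANOVA and Kruskal-Wallis tests are non-directional.

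On the two-sided reading, 69 randomised give 70.9% power after the stated loss and 75.6% without it. This rests on two assumptions: that 0.80 is d, and that the comparison is an unadjusted one between two groups at one visit. The documents do not allow the power of the planned mixed model to be stated.

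**What to change.** Keep 69 participants and rewrite the sample size paragraph. Name the test, its sidedness, the pairwise ODI contrast and the visit on which the calculation rests, and say that 0.80 is Cohen's d. Then do one of the following:

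- Restate the power: 23 randomised per group, 10% loss and two-sided alpha 0.05 give about 71% power for d = 0.80, and 80% power for d = 0.89.
- If the primary contrast is to be adjusted for baseline ODI, recompute the power with the baseline-to-follow-up correlation from the unpublished study of 50, if it is available there. With r = 0.5 the result would be about 83%, but that value is an assumption until the data confirm it.

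If a one-sided test was intended, the protocol should say so and the planned analyses should match it.

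The cost is one paragraph and, under the first option, a less favourable power statement. No extra participants are needed.

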**ASSE****SS****ME****NTS:**							
**Baseline demographic information**		**●**					
**Physical functioning** (ODI)		**●**		**●**	**●**	**●**	**●**
**Pain** (NRS)		**●**		**●**	**●**	**●**	**●**
**Pain-related fear** (TSK-11)		**●**		**●**	**●**	**●**	**●**
**Self-efficacy** (CDSES −6)		**●**		**●**	**●**	**●**	**●**
**Perception of change** (GRoC)				**●**	**●**	**●**	**●**
**Number of steps walked per day**			**●** (daily)				

A_0_: first contact with participants; A_1_: baseline assessment; I: 7-day intervention; A_2_: assessment 1 week after baseline; A_3_: assessment 4 weeks after baseline; A_4_: assessment 12 weeks after baseline; A_5_: assessment 24 weeks after baseline; ODI: ODI-French Canadian Version; NRS: pain numerical rating scale; TSK: 11-item version of Tampa Scale of Kinesiophobia; CDSES − 6: Chronic Disease Self-Efficacy Scale - Short-Version and GRoC: global rating of change

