#### Timeline

First visit: baseline measurements and intervention

*Baseline:* At the baseline assessment, demographic characteristics will be collected before participants complete self-administered questionnaires on symptoms and functional limitations (ODI-French Canadian Version) [15, 17], pain-related fear (11-item version of Tampa Scale of Kinesiophobia – TSK-11) [18] and self-efficacy measured with the Chronic Disease Self-Efficacy Scale - Short-Version (CDSES-6) [19]. Pain intensity will be measured using an 11-point numerical rating scale (NRS) [20, 21] (average previous week [1-week]). These 4 questionnaires will serve as outcome measures (see “Outcome measures” section). The STarT Back Screening Tool [22] and the Canadian minimal dataset for low back pain [23] will be completed to characterise the participants recruited. After baseline assessment*,* participants will be assigned randomly to one of three intervention programs.

*Intervention:* To start, participants will meet a physical therapist (PT) to receive their assigned program (60-min meeting). For participants assigned to the thermal therapy groups (thermal therapy alone and thermal therapy + exercises), a heatwrap (ThermaCare®, Pfizer inc., New York, USA) will be applied onto the lower lumbar spine area, whereas in participants assigned to the control group, a sham non-heat lumbar belt will be applied. In addition, the physical therapist will teach an exercise program to the participants assigned to the “thermal care + exercises” group.
2Intervention program

After the 1st visit, participants will take part in their assigned 7-day intervention program. Every day, participants will indicate in a logbook their average pain level during the day and the adherence to their program. A fitness watch will be given to each participant to record the number of steps walked per day during intervention week. They will be asked to avoid meeting a health care professional for their ALBP during the 7 day-intervention program. After the 7 days, they will be free to do so.
3Second visit – short-term follow-up

A 2nd visit will be realized approximatively 7 days after the 1st visit, and ODI, TSK-11, CDSES-6, average 1-week pain intensity and a global rating of change (GRoC) [24] will be measured to determine the short-term effect of thermal therapy.
4Long-term follow-ups

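### Perception of change (GRoC) has no week-0 value, so the planned Time levels do not match its schedule and the Group x Time interaction can miss a sustained benefit

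*Protocol article*

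**What the plan says.** Sample size & statistical analysis gives one model for everything: "Generalized linear mixed models (GLMM) will be performed for all outcomes". Its terms are fixed: "Our GLMM will incorporate terms for Group and Time (0, 1, 4, 12 and 24 weeks), and Group x Time interaction", with a random effect for participants. The term that carries the conclusion is also named: "The Group x Time interactions will inform if there is a benefit to combine both treatments". The only outcome given a different test is the step count (one-way ANOVA or Kruskal-Wallis).

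The description of GRoC does not fit this model. Under Secondary outcomes, perception of change "in global LBP condition since the initial assessment will be measured using a single-item question", so the score is itself a change from baseline. In Table 1 the GRoC row has marks at A2 to A5 and none at A1. Timeline agrees. After listing the disability, fear, self-efficacy and pain instruments completed at baseline, it says "These 4 questionnaires will serve as outcome measures", and GRoC is not among them. GRoC first appears at the second visit (about week 1) and then at weeks 4, 12 and 24.

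Objectives and hypothesis places perception of change in the principal objective. It expects the combination to do better than thermal therapy alone and control in both the short and the long term.

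**The concern.** For an outcome measured at baseline, randomisation makes the groups equal in expectation at week 0. A benefit that appears at week 1 and stays is then a change in the group difference over time, and the interaction detects it. GRoC has no such anchor. Its first value already contains the treatment effect, so a difference that is present at week 1 and persists does not change over time and sits in the Group term.

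The interpretive rule written for the baseline-measured outcomes therefore means something else for GRoC. It responds to a benefit that fades and not to one that lasts. The Background gives transfer of the short-term effect to the long term as the study's specific contribution, so a lasting difference is the pattern of most interest. At stake is the reading of one secondary outcome that belongs to the principal objective.

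**Working it through.** **Inputs from the article.** Three groups; Time levels 0, 1, 4, 12, 24 weeks; GRoC at weeks 1, 4, 12, 24; 23 per group; effect size 0.80, alpha 0.05, power 0.80, 10% loss.

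**Inputs assumed.** The article gives no SD or within-person correlation for GRoC. I take a 0.8 SD benefit (borrowed from the ODI sample size), thermal therapy alone equal to control, and correlations of 0.3, 0.5 and 0.7.

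**The plan's own figure.** A two-group normal formula, 2(z_alpha + z_beta)²/d², with one-sided alpha gives 2(1.645 + 0.842)²/0.64 = 19.3, so 20, and 20/0.9 = 22.2, so 23. The article does not state sidedness; two-sided alpha gives 25 and then 28. The figure serves here only as the group size, and the point does not depend on how it was reached.

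**Step 1: levels against data.** The stated model has 3 x 5 = 15 fixed-effect cells. GRoC fills 3 x 4 = 12, and the design matrix has rank 12. The three week-0 cells are empty by design, so the five-level model is not estimable for GRoC.

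**Step 2: what the interaction tests.** Let D(t) be the difference between two groups at week t. Interaction contrasts have the form D(t) − D(s).
- With a week-0 value, D(0) = 0 in expectation, so D(t) − D(0) = D(t). A lasting benefit appears in full.
- For GRoC, only differences among D(1), D(4), D(12) and D(24) remain. If all equal 0.8 SD, every contrast is 0.8 − 0.8 = 0 and power equals alpha. This is algebra and holds for any sample size or correlation.
- If D fades as 0.8, 0.5, 0.2, 0 SD, the largest contrast is 0.8 − 0 = 0.8 SD, while the average over follow-up is (0.8 + 0.5 + 0.2 + 0)/4 = 0.375 SD.

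**Step 3: size.** Balanced random-intercept data were simulated 5,000 times per setting and tested with split-plot F tests, which equal the mixed-model tests when data are complete. Rejection rates (%) with 23 per group, for correlation 0.3 / 0.5 / 0.7:

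| Setting | Group x Time | Group |
|---|---|---|
| GRoC, constant 0.8 SD | 4.9 / 5.1 / 5.5 | 98.4 / 94.1 / 88.4 |
| GRoC, fading 0.8, 0.5, 0.2, 0 SD | 50.3 / 68.3 / 91.2 | 45.4 / 34.8 / 29.5 |
| Outcome with a week-0 value, 0.8 SD from week 1 on | 63.9 / 80.8 / 96.8 | 92.3 / 81.0 / 72.5 |

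The simulation error at 5% is √(0.05 x 0.95/5000) = 0.3 percentage points, so the first row's interaction rates are consistent with alpha. With 21 per group (23 x 0.9 = 20.7) the constant-benefit row is 5.4 / 4.7 / 4.6 for the interaction and 97.7 / 91.8 / 85.7 for Group.

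The third row shows that the rule works where a baseline value exists. The second shows that the averaged Group effect is weak against a fading benefit, which favours visit-specific differences.

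**The case against.** The strongest reply has four parts.

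- **The Time list is the common visit schedule.** Table 1 and Timeline say plainly when GRoC is collected, so the sensible reading is the same model on four visits. This largely stands. A reader might infer that the GRoC analysis cannot be run at all, and the documents do not support that: software would drop the empty level and fit weeks 1 to 24. What remains is that the levels are misstated for GRoC, and that dropping week 0 leads directly to the interaction test examined above.
- **The Group term is already in the model.** This stands too. A reader might infer that a lasting benefit would be reported as no effect. That does not follow, because Group will be estimated and the article does not say it will be ignored. The article does, however, name the interaction as the evidence of benefit, and turning to Group after seeing the data would be a post hoc choice.
- **An exactly flat benefit is only one scenario.** Correct. The hypothesis speaks of short-term and long-term benefit, not of equal benefit, and the Discussion allows that heat may act only transiently. Against a fading benefit the interaction has partial power.
- **Outcome-specific detail belongs in a fuller document.** This would answer an omission. Here the article itself states the scope, the levels and the deciding term, and makes an exception for steps but not for GRoC. The nparLD fallback applies only if model assumptions fail, and it comes with no other Time factor or deciding term.

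A reader might also suppose that a constant 0 would be entered for GRoC at week 0. Nothing in the article proposes this, and no part of the point rests on it.

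**Conclusion.** The point holds for GRoC only. The stated Time levels do not match its schedule, and once week 0 is dropped the named test has power equal to alpha for a constant benefit and partial power for a fading one. A sustained benefit could be missed if the interaction alone is interpreted as planned.

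The power-equals-alpha result is exact for a flat difference. The other percentages rest on the assumed 0.8 SD, the assumed pattern, the assumed correlations and complete data; they illustrate the contrast and do not forecast this trial. ODI, pain, TSK-11 and CDSES-6 have week-0 values, so their analysis is unaffected, as is the sample size. The consequence is confined to one secondary outcome.

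**What to change.** Add to Sample size & statistical analysis that, for GRoC, Time has the levels 1, 4, 12 and 24 weeks. State that benefit is judged from prespecified between-group differences (combination against thermal therapy alone, and combination against control) at week 1 for the short term and week 24 for the long term, or from the Group effect averaged over follow-up. Keep Group x Time for GRoC only as a test of whether the difference changes over time, and apply the same rule if nparLD is used.

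Of the two options, the visit-specific differences match the stated hypothesis more closely and do not depend on the benefit being flat. Their price is power: one two-sided comparison at one visit, at 0.8 SD with 23 per group and no multiplicity adjustment, has about 76%.

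The cost is a sentence or two. No new data and no change to visits or sample size are needed, provided the choice is fixed before group comparisons are seen.

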**Methods/design:**

Sixty-nine participants with acute LBP will be randomly assigned to one of three intervention programs: 1) thermal therapy, 2) thermal therapy + exercises, and 3) control. The interventions will be applied for 7 continuous days. The primary outcome will be disability and secondary outcomes will be pain intensity, pain-related fear, self-efficacy, number of steps walked and perception of change. The evaluators will be blinded to the interventions, and participants will be blinded to other groups’ interventions. Primary and secondary outcomes will be compared between intervention groups.

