### Objectives and hypothesis

Our principal objective is to determine the effect of wearable continuous low-level thermal therapy combined or not with exercises on disability, pain intensity, pain-related fear, self-efficacy and perception of change in short-term (i) and long-term (ii) in adults presenting ALBP. Our secondary objective is to determine the effect of these interventions on the number of steps walked over the first week of treatment. We hypothesize that the combination of thermal therapy and exercises will have a larger positive effect for all outcomes (disability, pain intensity, pain-related fear, self-efficacy and perception of change) compared to thermal therapy alone and the control group in the short and long-terms. It will also be associated with a higher number of steps walked during the first week of treatment for the group receiving a combination of thermal therapy and exercises suggesting a higher level of physical activity.

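### Step counts fall outside the GLMM promised for all outcomes and get an unadjusted three-group omnibus test that cannot alone show the combined arm walks more, with the unit of analysis left open

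*Protocol article*

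**What the plan says.** All references are to the protocol article.

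- **Status of the outcome.** The Abstract (Methods/design) lists steps among the secondary outcomes: "secondary outcomes will be pain intensity, pain-related fear, self-efficacy, number of steps walked and perception of change". Under Objectives and hypothesis they make up the whole secondary objective: "Our secondary objective is to determine the effect of these interventions on the number of steps walked over the first week of treatment".
- **Hypothesis.** For the combined arm, the same section predicts: "It will also be associated with a higher number of steps walked during the first week of treatment".
- **Data.** Timeline: "A fitness watch will be given to each participant to record the number of steps walked per day during intervention week". Table 1 marks steps as daily, in the intervention column only. Each participant can therefore contribute up to seven values, and there is no pre-treatment value.
- **Model.** Sample size & statistical analysis: "Generalized linear mixed models (GLMM) will be performed for all outcomes". Its terms follow: "Our GLMM will incorporate terms for Group and Time (0, 1, 4, 12 and 24 weeks"), with a Group by Time interaction and a participant random effect.
- **Test for steps.** The same paragraph: "A one-way ANOVA or a non-parametric Kruskal-Wallis ANOVA will be used to compare the effect of intervention" on steps per day.
- **Stratification.** Randomization / blinding stratifies by sex and by ODI score (10 to 19, or 20 and above).

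**The concern.** The statement on the GLMM covers every outcome, yet one listed secondary outcome is given a different method in the same paragraph, and no exception is declared. The method given to steps has three weaknesses.

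1. A one-way ANOVA or Kruskal-Wallis test has group as its only factor, so the two stratifiers are left out.
2. It tests whether the three groups are all alike. The hypothesis is that one particular arm exceeds each of the other two.
3. It needs one independent value per unit. Steps per day could mean a participant's weekly average or the separate daily records, and the article does not say which.

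At stake is the answer to the secondary objective. A significant omnibus result could be read as support for the combined arm when it only reflects a difference between heat and control. If the daily records were entered as they stand, the p-value could not be trusted. The primary ODI analysis is not affected.

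**Working it through.** The article gives no figure for the step analysis, so there is none to reproduce. The 23 participants per group were sized on the ODI and are taken here as given.

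**1. Does the stated GLMM fit steps?** Its Time levels are 0, 1, 4, 12 and 24 weeks. Steps exist only for days within the first week. No step measurement corresponds to weeks 4, 12 or 24, or to a baseline at week 0. The model cannot apply, so the wording about all outcomes is literally wrong for steps.

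**2. Unit of analysis.** Inputs: 3 groups, 23 per group, 7 days, nominal level 0.05 (all from the article). The within-person correlation ρ of daily steps is not given; 0 to 0.7 is assumed.

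- Records if days are pooled: 3 × 23 × 7 = 483.
- Design effect: 1 + (7 − 1)ρ.
- Approximate type I error of the pooled F test with 2 numerator degrees of freedom: exp(−3.01 / design effect), where 3.01 is the 5% critical value.
- Check by simulation: 10,000 null trials per value of ρ, exchangeable correlation.

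| ρ (assumed) | Design effect | Pooled days, formula | Pooled days, simulated | One mean per participant, simulated |
|---|---|---|---|---|
| 0 | 1.0 | 0.05 | 0.050 | 0.048 |
| 0.3 | 2.8 | exp(−1.075) = 0.34 | 0.347 | 0.048 |
| 0.5 | 4.0 | exp(−0.753) = 0.47 | 0.486 | 0.052 |
| 0.7 | 5.2 | exp(−0.579) = 0.56 | 0.569 | 0.052 |

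The same test is valid under one reading and badly anti-conservative under the other.

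**3. Omnibus test against the hypothesis.** Simulation with one value per participant, 23 per group and 10,000 trials. The standardised means are assumed, in the order control / thermal / combined. The last column counts trials in which the combined arm is higher than both other arms, each with two-sided p < 0.05.

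| Assumed means | Omnibus test rejects | Combined beats both |
|---|---|---|
| 0 / 0.8 / 0.8 | 79% | 2% |
| 0 / 0.4 / 0.8 | 66% | 25% |
| 0 / 0 / 0.8 | 78% | 62% |

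In the first row exercise adds nothing to heat, so the hypothesis is false, yet the omnibus test is significant in about four trials out of five. The first and third rows show nearly the same rejection rate for opposite answers to the question asked.

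**4. Stratifiers.** A one-way layout has no place for sex or ODI category. If either predicts walking, its variation stays in the error term and the group comparison loses precision. The article gives nothing from which to put a number on that loss.

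**The case against.** A reader might infer that the plan ignores the seven repeated days and so runs a test with a false-positive rate of 35% or more. The article does not support that. It nowhere says that daily records enter separately. Steps per day is a common way to express a participant's average, the objective is framed over the week as a whole, and a one-way test presupposes one value per person. On that reading, type I error is about 5%. This objection stands, and the inflated figures hold only if days are pooled.

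It is also fair to say that an average loses little. With seven days from everyone, the participant-mean analysis and a random-intercept model give essentially the same group test. With missing days, the variance of a person's mean is proportional to ρ + (1 − ρ)/m. At ρ = 0.30, a two-day participant should carry (0.30 + 0.70/7) / (0.30 + 0.70/2) = 0.40/0.65 = 62% of the weight of a seven-day participant; at ρ = 0.60 it is 0.657/0.80 = 82%. Equal weighting is a modest inefficiency, and nothing suggests that two-day records will be common.

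The conflict over all outcomes can be read as a drafting slip, since the later, specific sentence works as an exception. Pairwise contrasts and rules for valid days are commonly left to an analysis plan that is not shown. Both points lower the weight of the finding. They do not remove it: the article names a particular test for steps, that test has no covariates by construction, and it is the only step analysis offered in answer to a hypothesis about one specific arm.

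**Conclusion.** The point holds in limited form. The section contradicts itself on which outcomes get the GLMM. The test it names for steps is an unadjusted omnibus comparison that omits both stratifiers and cannot alone establish that the combined arm walks more. In the assumed case where exercise adds nothing to heat, it would still be significant in 79% of trials, against 2% in which the combined arm beats both others.

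The unit of analysis is open. Type I error is about 5% with one mean per participant and about 35% to 57% with pooled days. The second range depends on assumed correlations of 0.3 to 0.7 and on a reading that the article does not state. It is a reason to fix the wording and does not show that the planned analysis is invalid.

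This concerns a secondary outcome. It is worth correcting because the whole secondary objective rests on it and the change is easy.

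**What to change.** Change the analysis section as follows.

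- State that the five-time-point GLMM applies to all outcomes except steps.
- Analyse daily steps with a linear mixed model: fixed effects for Group, study day, sex and ODI stratum, and a random participant effect. This also uses every recorded day when some are missing. Equivalently with complete data, use an ANCOVA on each participant's mean steps per recorded day, adjusted for sex and ODI stratum. Name one of the two, so that the unit of analysis is settled.
- Report combined versus thermal therapy alone and combined versus control as mean differences in steps per day with 95% CIs, in place of the omnibus p-value.

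The data are already collected daily and both stratifiers are known at randomisation, so no extra measurement or participants are needed. The cost is a wording change and slight extra analysis work.
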